## Abstract

**Background:**

Training and body composition requirements in elite sports may elevate eating disorder (ED) risk. Current estimates suggest a range of 1–28% prevalence of ED in elite athletes, reflecting methodological heterogeneity, underreporting, and limited research focus. EDs adversely affect physical health (e.g., osteoporosis, fatigue, injury), psychological well-being, and athletic performance, often persisting beyond athletic careers. Sport-specific demands may obscure ED symptoms, making underdiagnoses likely. This longitudinal study’s objective is to furnish proof for the theoretical model of disordered eating in elite athletes by examining the role of sport-specific indicators, to improve early identification and psychological diagnostics.

**Methods:**

Three-hundred elite athletes from weight-sensitive (ballet, bodybuilding) and less weight-sensitive (soccer, racket sports, basketball) sports will complete assessments at four time points. A subgroup of 90 athletes will participate in clinical interviews. Logistic and hierarchical regressions will identify ED risk indicators and estimate the prevalence of EDs in athletes. Receiver Operating Characteristic (ROC) analyses will assess diagnostic accuracy of single and combined indicators with reporting of sensitivity, specificity, and the Area Under the Curve (AUC). Group differences and measurement invariance of ED instruments will be tested between the athlete group and 300 non-athlete controls.

**Discussion:**

Identifying reliable ED indicators in elite sports may support early intervention. This theory-based approach aims to enhance diagnostic accuracy and athletes’ care.

**Trial registration:**

Prospective registration of the study in the German Clinical Trials Register (DRKS00035100) on 03 February 2025.

**Supplementary Information:**

The online version contains supplementary material available at 10.1007/s44192-026-00544-y.

## Background

Psychological distress in elite athletes gains increased attention in both media coverage and scientific debate [1]. New screening instruments such as the Sport Mental Health Assessment Tool [2] were developed by the International Olympic Committee to better identify athletes at risk for mental health symptoms and allow timely support for athletes [3, 4].

Since eating disorders (EDs) in athletes have a negative impact on health, for example by leading to osteoporosis, higher injury rates, amenorrhea, fatigue, and performance decline [5–8], research on the psychopathology of EDs seems inevitable. The onset of EDs mostly occurs in puberty, which endangers a proper physical development [9]. Affected athletes show high comorbidities with affective-, anxiety- and substance use disorders [10]. ED symptoms often become chronic, leading to health restrictions, direct (e.g. hospitalization, medication) and indirect (e.g. societal production deficit due to premature death, symptom-driven food expenses) health economic costs and a reduced quality of life, even beyond the end of an active career [3, 11]. Early identification is crucial to prevent both performance loss and symptom chronicity.

EDs are reported in 1% to 28% of elite athletes [3], a variability that likely reflects methodological heterogeneity, underreporting, and limited research focus [12]. In addition, elite athletes may express disordered eating (DE) through differential phenotypes, with DE defined as maladaptive eating behaviors and cognitions that do not meet diagnostic criteria for an ED in terms of frequency, duration, or clinical severity [13–15]. Those DE patterns might be influenced by training status, sport discipline, or energy availability. These complexities underscore the need for a multidimensional approach to identify affected athletes [16]. A theoretical model for the psychopathology of EDs in elite sports was developed based on existing knowledge and evidence [16]. It expects the indicators *weight-sensitivity* of the sport-discipline, *weight and shape pressure*, *internalisation of a sports discipline-specific body ideal*, *unhealthy training behaviours and intentions*, and *fatigue* to potentially enhance the probability to have an ED as an athlete [16].

The model considers that athletic success and health risks often coexist in elite sports [17]. Elite athletes face the challenges of adhering to sport-specific eating, and nutritional and training habits to create optimal physical conditions for their high training requirements [16, 17]. Particularly in weight-sensitive sports disciplines (e.g., bodybuilding, ballet dance), the sport context dictates specific body images or weight goals that pressure elite athletes to follow certain dietary and training practices for their health and athletic success [17, 18]. Research in non-athletes on muscularity-oriented behaviours has the potential to improve diagnostic practices in men [19]. These insights may also aid at identifying DE in both men and women athletes, as elite sports place emphasis not only on thinness but also on the targeted modification of body composition, muscularity types, and specific body areas, regardless of sex [20].

In some sports disciplines, periods of *Adaptable Low Energy Availability* (adaptable LEA) or *Functional Overreaching* are used to enhance athletic performance, whereby athletes modulate their body weight or challenge their athletic limits before restoring sufficient energy availability or recovery [4]. Hunger does not reliably reflect the elevated energy and nutritional needs of physically active individuals, making athletes prone to inadvertent energy deficits [21], especially when nutrition knowledge is not sufficient [22–24]. In addition, the reinforcement athletes receive within the sport context for internalising body images by aligning their eating and training habits, may promote DE [25–27] and other health-compromising practices such as obsessive healthy eating [28], or the use of anabolic steroids [29]. If training load is not compensated with nutritional energy or regeneration, then mental, endocrine, and metabolic health impairments can occur [30, 31], described as *Relative Energy Deficit in Sport* (RED-S) or *Overtraining Syndrome* (OTS). Each syndrome has traditionally focused on either nutritional or recovery-related aspects; however, recent research has demonstrated substantial overlap in their etiology, symptom presentation, and diagnostic characteristics [32]. Previous approaches investigated potential physical markers for RED-S or OTS [33, 34], e.g., increased visceral fat in combination with hormone imbalances [35]. Diagnosis of these syndromes remains challenging due to heterogeneous symptom presentations [36, 37]. Fatigue is a key symptom, often accompanied by reduced performance and psychological strain [21, 26, 38, 39].

As the consequences of eating and training regimes can be both protective and damaging [31], DE may remain undetected or misinterpreted as sport-typical behaviour [16]. Conventional diagnostic criteria might especially be ineligible to diagnose EDs in elite athletes, as those are not tailored to sport-specific requirements [40]. While the above-mentioned model of [name] and colleagues has yet to be empirically tested, it may function to fill this research gap by providing a promising, evidence-based approach for the use in sport-specific healthcare and clinical practice.

### Objectives

The *primary objective* of the study is to evaluate the validity of the model for pathological eating in elite sport [16]. The indicators (weight-sensitivity, weight- and shape pressure, internalisation of a sports discipline-specific body ideal, unhealthy training intentions and behaviour, fatigue) specified in the model are expected to explain variance in ED symptomatology (measured by EAT-26) and/or increase the likelihood of an ED (clinical interviews) in elite athletes. The *second aim* is to investigate whether the diagnostic accuracy of ED identification in elite sports can be improved by combining standardized instruments (e.g., EAT-26) with sport-specific indicators (e.g., ART). The goal is to empirically derive cut-off scores that prioritize high sensitivity to minimize the risk of false negatives, while maintaining acceptable levels of specificity. The *third aim* is to estimate the prevalence of EDs in elite athletes by both the number of diagnosed cases in this cohort and ED instruments. The prevalence in weight-sensitive sports disciplines is hypothesised to be higher compared to less weight-sensitive sport-disciplines and compared to a control group. *Further study objectives* are the identification of protective factors (e.g., sport type, nutrition knowledge) for DE, the investigation of the predictive validity of the indicators, and the association of physiological markers (e.g., body fat percentage) with DE in elite sports. Methodologically, this study aims at investigating whether conventional instruments measure ED symptoms differently in elite athletes than in the control group.

## Materials and methods

To the best of our knowledge, there is no specific guideline available for reporting study protocols of longitudinal diagnostic accuracy studies [41]. Given this is a non-interventional, diagnostic accuracy study, the “Standards for Reporting of Diagnostic Accuracy Studies” [42] guidelines served as the best available alternative to prepare this study protocol. Prior to recruitment (03 February 2025), the study had been registered at the German Clinical Trials Register (DRKS00035100). If important changes are made to the study protocol, the ethics committee will be informed, and the registration of the study will be updated.

### Study design and procedure

ENHANCE (Eating and Nutritional Habits in Athletes and Controls — a longitudinal Examination) is a prospective, non-interventional, longitudinal study combining quantitative assessments and semi-structured clinical interviews to evaluate the validity of our previously published theoretical model [16] and assess the prevalence of EDs among elite athletes, including a non-athlete control group for comparative analysis. At four assessment points (T0 – T3, see Fig. 1), sociodemographic, health, training, nutritional, and psychological data will be collected via digital assessments (created with Unipark software, Tivian XI GmbH) as self-reports from both the athlete and non-athlete group. Additionally, a subgroup of athletes will be invited to participate in clinical interviews and body measurements.

**Fig. 1 Fig1:**
[figure not shown]
Flow chart of the study. Notes: T0: Baseline assessment, T1-T3: Time points for follow-up assessments, ED: Eating disorder, blinded: Regarding the scores of the index tests

After providing electronic informed consent, participants can access an eligibility screening by following the study link. Based on the eligibility screening, the participants are assigned to either the elite athletes or the control group, or will be excluded from the study (see section participant eligibility and recruitment). After completing the baseline assessment, controls can exit the survey, while elite athletes will be forwarded to an appointment booking system. There, they can optionally schedule an appointment for a clinical interview (online or in person, in German or English) and/or the body measurements approximately one month after baseline assessment. Trained specialists will conduct the clinical interviews and body measurements. Body measurements (i.e., body fat percentage) can also be conducted by an external health care professional chosen by the participant. Interview and body data are documented in an electronic case report file. Links to access the follow-up assessments are send via email by the study staff. All emails and reminders are standardized. Data of each assessment point will be linked using pseudonymized participant codes.

### Participant eligibility and recruitment

All participants are required to speak and understand English fluently to be included in the study. This study is aimed at elite athletes who (a) practice either ballet, bodybuilding, racket sports, soccer, or basketball, (b) organise their daily life around their sport and (c) regularly participate in competitions or performances [1, 13, 36, 43, 44]. To be assigned to the elite athlete group, the training must have been practiced for at least six months with more than 300 min/week at moderate or higher intensity [36]. Participants, who fulfil the criteria for classification as elite athletes and practice one of the sports disciplines mentioned above, are included in the elite athletes group. Participants who do not meet the criteria of the elite athlete group are assigned to the control group. Participants in the control group may also train regularly but should not match the elite athletes’ criteria. If the participants fulfil the criteria to be considered elite athletes, but do not practice any of the sports disciplines examined in this study, they will be excluded from the study.

Participants are recruited purposefully at sports facilities, sports boarding-houses, ballet academies, ballet companies, sports clubs, fitness fairs, sports events, and on social media. Among other recruitment strategies, we search Instagram accounts affiliated with ball sport-, ballet-, or bodybuilding associations like the International Federation of Bodybuilding and Fitness. Moreover, ballet companies or academies are contacted to inform potential eligible participants about the study and distribute the recruitment material.

A screening prior to baseline assessment enrols eligible participants. They will be asked to provide their contact details in a survey link separate from study data, which is used to contact participants one, six and twelve months after baseline assessment for follow-up assessments (see Table 1.). Participation in the clinical interviews is voluntary for the athlete group.

**Table 1 Tab1:** Assessment Schedule

				Planned assessment time points								
				Athletes					Controls			
Criteria				T0	T1	T2	T3		T0	T1	T2	T3
	*Eating disorder (A) and Disordered eating (B)*											
			Clinical interviews		X							
			Eating Attitudes Test-26	X		X	X		X		X	X
			Eating Disorder Examination Questionnaire		X					X		
			Brief Eating Disorder in Athletes Questionnaire	X	X	X	X		X	X	X	X
Indicators				T0	T1	T2	T3		T0	T1	T2	T3
		*Weight and shape pressure (E)*										
			Weight Pressure in Sport in Males/ Females	X			X					
		*Body image (F)*										
			Muscle Dysmorphic Inventory	X			X		X			X
			Subscale Drive for Thinness Eating Disorder Inventory 3	X			X		X			X
		*Training habits (G)*										
			Athletes’ Relationships with Training Scale	X		X	X					
			Rating of Perceived Exertion	X	X	X	X		X	X	X	X
		*Fatigue and mood disturbances (H)*										
			Profile of Mood Scale	X			X		X			X
			Rating of Fatigue	X	X	X	X		X	X	X	X
			Endocrine and Metabolic Responses on Overtraining Syndrome Tool	X								
			Low Energy Availability in Females/ Males	X		X*	X*		X*		X*	X*
Other measurements				T0	1T	T2	T3		T0	T1	T2	T3
		*Nutritional knowledge and obsessive healthy eating (I)*										
			Abridged Nutrition for Sport Knowledge Questionnaire		X					X*		
			ORTO-Revised version		X					X		
		*Psychological strain (J)*										
			Athlete Psychological Strain Questionnaire	X	X	X	X					
			Patient Health Questionnaire 4	X	X	X	X		X	X	X	X
		*Body measurements (K)*										
			Bioimpedance analysis, blood pressure, heart rate, oxygen saturation	X		X	X					

Notes: TO: Baseline assessment, T1-T3: Follow-up assessments. *ORTO*: Instrument measuring orthorexic thoughts and behaviours. X *: Only assessments of selected subscales. Controls only fill in non-sports-specific items. Body measurements: Body mass index, heart rate, blood pressure, oxygen saturation, waist-hip ratio and body composition. Letters in brackets: In reference to the order in section 2.3. Outcome measures

### Outcome measures

The primary outcome is the additional variance explanation in the psychopathology of eating behaviour in the elite sports group by the indicators (∆R²) of our theoretical model of DE [16]. The criteria of the regression models will be measured (A) binary conducting clinical interviews (ED present or absent) and (B) continuous using an ED instrument (severity of ED symptomatology).

*A)* Clinical interviews serve as a reference test. Trained specialists will assess participants for EDs (anorexia nervosa, bulimia nervosa, binge-eating disorder, and others) using ICD-11 criteria [14] in a ~ 30-minute interview. Based on the indicator internalization of a sport-specific body ideal, including muscular body images that can potentially contribute to EDs in elite sports, the criteria for muscle dysmorphia proposed by Pope et al. [45] are also part of the interview. ICD-11 criteria will be evaluated using selected questions of the ED examination interview from Lichtenstein et al. [26], allowing a sports-specific exploration of the fear of weight gain or behaviours to prevent weight gain, weight and shape concerns, food-related loss of control, exercise behaviour, and compensatory behaviours. Additionally, performance enhancing substance use, obsessive healthy eating, and physiological consequences of low energy availability in elite sports like reduced sex drive or menstrual dysfunction are evaluated [26, 46, 47]. In addition to the identification of EDs associated with clinically relevant psychosocial and physical impairments, borderline cases will be documented as DE presentations [48]. In comparison to the ICD-10, the ICD-11 might facilitate diagnosis in men by removing the endocrine disorder criterion [14]. Neither the interviewers nor the participants are informed about the results of the index tests.

*B)* The Eating Attitudes Test 26 [EAT-26; [49] evaluates the frequency of DE behaviours on a 6-point-scale with a cut-off of 12.66 indicating clinical risk in athletes [50, 51]. The EAT-26 is administered at T0, T2 and T3 and is used as a measure of ED symptom severity in the hierarchical regression analyses.

Self-reported DE will also be assessed by the Eating Disorder Examination Questionnaire [EDE-Q, [52] in both groups and by an additional third instrument only in the elite athlete group. The EDE-Q is a valid and reliable EDs instrument with 28 items and four subscales (restraint, eating concern, weight concern, shape concern). Participants indicate the frequency of eating behaviours over the past 28 days. In a Danish elite athlete cohort, the EDE-Q showed 90% sensitivity and 100% specificity with a cut-off of 2.3 [26]. The Brief Eating Disorder in Athletes-Questionnaire [BEDA-Q; [40] is validated for women athletes and consists of nine items indicating DE with a cut-off of 4 [40]. The first six items are adopted from the Eating Disorder Inventory 2 EDI-2 [53] and can be rated on a 6-point-scale. The three last items capture dieting regimes and frequency. The area under the curve (AUC) was 0.73 (98% CI, 0.52–0.93). Overlapping items of the instruments (e.g., Item 11 in the EAT-26 is the item 2 in the BEDA-Q and item 32 of the EDI-3) are only assessed once per survey. Both the EDE-Q and the BEDA-Q are used to assess the convergent validity of the EAT-26. They are not included as model criteria due to differences in assessment time points and item overlap with other instruments operationalising constructs in the theoretical model.

The regression models’ predictors consist of (C) sociodemographic-, health-, and sport-specific data, (D) the weight-sensitivity of the sports discipline, (E) the athletes’ perception of weight and shape pressure, (F) the internalisation of sport-specific body ideals (drive for thinness and muscularity striving behaviour), (G) training load, intentions and behaviours, and (H) the experience of fatigue and mood disturbances.

*C)* Sociodemographic data comprise sex, gender, age, nationality, occupation, and financial situation. Health data includes previous counselling or treatments and previous ED diagnoses. As the study targets elite athletes, the surveys include self-developed sport-specific items for elite athletes, such as sports discipline, current intention to modulate body weight, training phase and amount in their sports discipline. Controls are asked to report general training frequency and duration. Both groups indicate nutritional and movement data in general.

*D)* The classification of weight-sensitivity into weight-sensitive (ballet) and less weight-sensitive (ball games) sports are adopted from Martinsen and Sundgot-Borgen [12]. The authors do not classify bodybuilding, but in this study it is considered a weight-sensitive sport, as the evaluation of physical appearance is regarded as the athletes’ performance [54, 55].

*E)* The Weight pressure in Sport Scale for men athletes [WPS-M; [56] and for women athletes [WPS-F; [57] are instruments that assess pressures from coaches and peers and include subscales specific to sex with 16 items for women and 14 items for men rated on a 6-point scale. In this study, items with the term “team members” is changed to “sport colleagues”, as most of the sports disciplines included in this study are individual sports.

*F)* Internalisation of body ideals is assessed by two validated instruments. The Muscle Dysmorphic Disorder Inventory (MDDI) measures the internalisation of a muscular body ideal [MDDI; [58] and includes 13 items across three subscales rated on a scale from 1 (never) to 5 (always). Based on the suggestion of Compte et al. [59], item five (“I think my chest is too small”) is adjusted to “I think my chest (muscle) is too small” to avoid the reference to breast volume [59]. The MDDI was used in an elite athlete cohort with men and women, showing good internal consistency (Cronbach’s α = 0.824), and categorizing individuals with scores ≥ 39 at risk for muscle dysmorphia [60, 61]. The internalisation of a thin body ideal is measured by the subscale of the Eating Disorder Inventory 3 Drive for Thinness [DT; [62, 63], which consists of 7 items rated on a scale from 0 (= never) to 5 (= always). Scores > 14 are considered as high DT [64]. EDI-3 items for weight history are used.

*G)* Training intentions and behaviour among athletes are measured with the Athletes’ Relationships with Training Scale [ART; [65] consisting of five subscales. Items 1–9 are rated on a scale from 1 (never) to 5 (always) and items 10–15 are rated on a scale from 1 (strongly agree) to 5 (strongly disagree). Scores ≥ 48 are considered as attitudes indicating DE. Additionally, training intensity on average over the last week is measured by a modified instruction for the Rating of Perceived Exertion [RPE; [66–70]. This single item scale assesses subjective physical effort on a scale from 1 (light activity) to 10 (maximal effort activity). Classification into easy (RPE ≤ 3), moderate (RPE 4–6), and hard (RPE ≥ 7) training intensity followed the suggestions of Ieno et al. [71].

*H*) Experience of fatigue as symptom of RED-S is measured by modified versions of the Low Energy Availability in Males Questionnaire [LEAM-Q; [46] and its counterpart for women, the Low Energy Availability in Females Questionnaire [LEAF-Q; [47]. Both instruments are self-report measures designed to detect physiological symptoms indicative of LEA in athletes. In the present study, selected sections.  (1, 2, 4, and 5) from the full LEAM-Q are administered to both men and women athletes. LEAF-Q subscales are included to collect use of contraceptives, and menstrual history and dysfunction in women athletes [47]. The pictorial rating of fatigue scale [ROF; [72] measures fatigue with response rates from 0 (not fatigued at all) to 10 (total fatigue & exhaustion- nothing left). The ROF scale can be used in the sports context to monitor athletes’ regeneration and ability to perform. Fatigue as symptom of Overtraining is assessed with the Endocrine and Metabolic Responses on Overtraining Syndrome clinical tool [EROS; [36]. The instrument consists of nine parameters [3 items on nutritional information, 4 Profile of mood states items, 2 items on performance impairment, and 1 item on sleep quality; 74], which adds up to a score that rules out OTS (0–2), remains inconclusive (3–5), or diagnoses OTS (6–9). Overlapping items with other scales are only assessed once. Mood disturbances are assessed by a short form of the profile of mood states [POMS; [73]. The questionnaire consists of 40 items with subscales rated on a scale from 0 (not at all) to 4 (extremely). The POMS was used in elite athlete cohorts to evaluate psychological distress, subjective training response, and exhaustion [74].

Except for the regression model’s predictors and criteria, *secondary outcomes* like (I) nutritional knowledge, obsessive healthy eating, sport-specific eating motives, and (J) psychological strain are assessed. Moreover, the elite athletes can participate in (G) body measurements.

*I)* The Athlete Nutrition Sport knowledge Questionnaire [ANSQK; [75, 76] measures general and sports nutrition knowledge with 37 items [75]. Overall, the ANSKQ is considered a reliable and valid measurement in which participants evaluate their weight management, macronutrients, micronutrients, supplementation, sport nutrition, and alcohol [75]. The ORTO-R [75, 76] is a revised version of the ORTO-15 to measure orthorexic thoughts and behaviours with six items rated on a four-point-scale [77–80]. The ORTO-R has been used in a sample of competing athletes showing measurement invariance in comparison with participants less active [81]. Sport-specific eating and nutritional behaviour is assessed with self-developed items.

*J)* The Athlete Psychological Strain Questionnaire (APSQ) measures psychological strain in elite athletes [82] with ten items [83] rated on a scale from 1 (none of the time) and 5 (all of the time). APSQ scores of ≥ 20 are considered as ‘very high’ psychological strain [83]. The Patient Health Questionnaire (PHQ) is a validated 4-item instrument, which measures severity of depressive symptomatology and anxiety with PHQ-2 ≥ 3 as risk for depression and GAD-2 ≥ 3 as risk for anxiety [84, 85].

*K)* The body measurements include the BMI (kg/m²), body composition, waist-hip ratio, blood pressure, and heart rate. The BMI assesses the nutritional status in adults and serves as a diagnostic criterion for EDs according to ICD-11 [86]. In adults, a BMI between 18.5 and 24.9 kg/m^2^ is considered as normal weight [87]. If participants do not undergo the body measurements, the BMI will be calculated from a self-report of the participant’s current body height and weight. A Seca mBCA 515 scale (Bioimpedance analysis) in the Clinic for Psychosomatic Medicine and Psychotherapy, LVR-University Hospital Essen (Germany) is used to measure body composition including fat-free mass, skeletal muscular mass, total body water, extracellular water, visceral fat, and body fat percentage adjusted for age, ethnicity, and gender to consider nutritional behaviour and needs over time [88], and physiological indicators of OTS symptoms [35]. The Seca scale uses Physical activity levels (PAL) to calculate total energy expenditure. As athletes move more than non-athletes, we derive PAL values from the participant’s basal energy expenditure and the Metabolic Equivalent of Task values for minutes of selected activities executed per day averaged over a week [89]. Systolic and diastolic blood pressure is measured with a digital blood pressure monitor (model name: Boso Medicus X Blood Pressure Monitor with All Basic Functions) after ten minutes of sitting. The oxygen saturation and heart rate (beats per minute) will be assessed with a pulse oximeter (from UEBE Medical GmbH, model: visomat PO_50_) at rest. Scales and devices from external health care professionals may vary, which will be documented.

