### Ethics, dissemination, and data protection management

This study has been approved by the Ethics Committee of the University Duisburg-Essen (24-12041-BO). Data collection, storage, and analysis follow the General Data Protection Regulation [98] regulations and the standard operating procedures of the LVR-University Hospital Essen, Germany.

This is a survey-based study supplemented by optional, voluntary clinical interviews and body measurements. No physical or psychological risks are anticipated. Participants receive detailed study information, including data protection, the voluntary nature of the study, and compensation before providing digital informed consent. In case an ED or clinically concerning low body weight are detected, participants will be offered counselling and treatment options through the Clinic for Psychosomatic Medicine and Psychotherapy, LVR-University Hospital Essen, Germany. Study staff is trained in confidentiality and data protection. The study is conducted in accordance with the ethical principles outlined in the Declaration of Helsinki [99]. Pseudonyms link data across assessment points. To protect data while enabling sample size tracking and follow-up assessments, a separate list includes pseudonyms, contact details, participation dates, and group assignments. This list is kept apart from the study data. Results will be shared via peer-reviewed journals, conference presentations, and with relevant stakeholders. Key findings will also be published in lay terms online and promoted through social media.

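### The T1 survey and the clinical interview fall in the same month with no stated order, so some athletes may answer the EDE-Q, given only at T1, after the interview

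*Protocol article*

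**What the plan says.** All references are to the protocol article; no separate analysis plan is shown.

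- **Reference standard and blinding (Outcome measures, A).** "Clinical interviews serve as a reference test". The blinding statement is "Neither the interviewers nor the participants are informed about the results of the index tests". The note to Fig. 1 gives the same scope: "blinded: Regarding the scores of the index tests".
- **Interview timing (Study design and procedure).** After the baseline survey, athletes may book "an appointment for a clinical interview (online or in person, in German or English) and/or the body measurements approximately one month after baseline assessment".
- **T1 survey timing (Participant eligibility and recruitment).** Contact details are collected separately, "which is used to contact participants one, six and twelve months after baseline assessment for follow-up assessments". Study staff e-mail the links.
- **Schedule (Table 1).** The interview and the EDE-Q appear at T1 only. The BEDA-Q appears at T0, T1, T2 and T3. The EAT-26 and the ART appear at T0, T2 and T3. Controls also complete the EDE-Q at T1 and have no interview.
- **Role of the questionnaires (Outcome measures, B).** "Both the EDE-Q and the BEDA-Q are used to assess the convergent validity of the EAT-26". They are not used as regression outcomes.
- **Analyses (Planned data analysis).** ROC analyses cover single and combined instruments without naming them. Measurement invariance of the eating disorder instruments is tested between athletes and controls.
- **What follows a detected disorder (Ethics, dissemination, and data protection management).** "In case an ED or clinically concerning low body weight are detected, participants will be offered counselling and treatment options". No timing is given.

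**The concern.** The stated blinding protects the interview from the questionnaire scores. For a self-report questionnaire the respondent also acts as the reader of the test, so the opposite direction matters as well. An athlete who has just spent about 30 minutes discussing weight and shape concerns, loss of control and compensatory behaviour may answer a 28-day questionnaire on the same themes differently. An athlete who has also been offered counselling has in effect learned the reference result, and may then report more symptoms or fewer.

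Three uses of the EDE-Q could be touched: its accuracy against the interview, its agreement with the EAT-26, and its invariance between athletes and controls. In the last two, only some athletes carry the exposure and no control does. Because the EDE-Q is scheduled only at T1, no earlier score can replace one given after the interview.

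**Working it through.** The plan states no figure on this point to reproduce. The check is a reading of the schedule, followed by arithmetic for scale.

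**1. Which instruments are exposed (Table 1, athletes)**

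| Instrument | Time points | Score before the interview assured? |
|---|---|---|
| EDE-Q | T1 | No |
| BEDA-Q | T0, T1, T2, T3 | Yes, T0 |
| EAT-26 | T0, T2, T3 | Yes, T0 |
| ART | T0, T2, T3 | Yes, T0 |

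The weight pressure scales, the muscle dysmorphia inventory, Drive for Thinness and the mood scale are also taken at T0. The ORTO-R is given only at T1, but it is a secondary outcome with no stated accuracy role. The exposure therefore comes down to the EDE-Q.

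**2. How many athletes**

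- Interviewed: 90 of 300 (Abstract), so 90/300 = 30%, and 210 athletes (70%) are in the same position as controls.
- Expected cases at the 30% prevalence in Sample size calculation: 90 × 0.30 = 27. That is 27/300 = 9% of the athlete group who could learn of a diagnosis, even if every interview came first.
- The share of the 90 who would answer T1 after the interview is not given and could be anywhere from 0 to 100%.

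In the invariance and convergent-validity analyses the exposure is diluted to at most 30% of athletes. In a ROC analysis it is not diluted, because every athlete with a reference result has been interviewed.

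**3. What one changed answer does to sensitivity**

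Each case whose EDE-Q classification changes moves sensitivity by 1/27 = 3.7 percentage points. At 28% prevalence there are about 25 cases and the step is 1/25 = 4.0 points.

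**4. What a shift does to the AUC (assumed inputs)**

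Assume an EDE-Q AUC of 0.80 under equal-variance normal scores. The separation is d = √2 × z(0.80) = 1.19. Let cases who answer after the interview shift by 0.3 SD, with non-cases unchanged:

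- Upward: Φ((1.19 + 0.3)/1.414) = 0.854.
- Downward: Φ((1.19 − 0.3)/1.414) = 0.735.
- Half of cases affected: (0.80 + 0.854)/2 = 0.827, or (0.80 + 0.735)/2 = 0.768.

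If the shift comes from the conversation itself and applies equally to cases and non-cases, half of each affected, the AUC is 0.5 × 0.80 + 0.25 × 0.854 + 0.25 × 0.735 = 0.797, practically unchanged. The bias therefore depends on a shift that differs between cases and non-cases.

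**5. Against sampling error**

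With 27 cases and 63 non-cases, the Hanley-McNeil standard error at AUC 0.80 is about 0.056, a 95% interval of about ±0.11. A bias of about 0.03 is roughly half a standard error.

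**The case against.** - **The order may be fixed elsewhere.** Fig. 1 is not shown, and an article may leave visit-level sequencing to the full protocol. This stands as a caveat. The figure note that is visible still limits blinding to index-test scores, and the article gives both timings without linking them.
- **Disclosure before T1 is an inference.** A reader might conclude that athletes answer the EDE-Q knowing their interview result. The documents do not support that as a settled sequence. They mention an offer of counselling when a disorder is detected, give no timing, and describe no feedback to athletes without one. What stands is that it can happen, mainly in positive cases.
- **The EDE-Q may not be an index test.** Its stated role is convergent validity. Combined tests are built from significant regression indicators, which it never enters. It could still be among the single instruments, since the ROC section names none and does not exclude it. The accuracy concern is conditional on that.
- **Accuracy as a whole might seem compromised.** It is not. The EAT-26, the ART and a first BEDA-Q precede the interview.
- **The numbers are assumed.** This is correct. The documents support neither the 0.3 SD nor the one-half share.
- **A strict fix has its own cost.** Making the interview conditional on a submitted survey could lose interviews among athletes short of time, and a questionnaire completed at the start of the appointment could prime the interview. Both points are fair and shape the fix below.

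**Conclusion.** The point holds in limited form. In the text shown, nothing prevents an interviewed athlete from completing the EDE-Q after the interview, and blinding does not cover that direction. EDE-Q accuracy could be biased if the EDE-Q enters the ROC analyses. Its convergent validity with the EAT-26 and its athlete-control invariance test could be biased to a smaller degree, with at most about 90 of 300 athletes exposed. Direction and size are unknown; the AUC range of about 0.77 to 0.83 around 0.80 only illustrates one set of assumptions. The primary regressions and the accuracy of the EAT-26, the ART and the BEDA-Q are not affected, provided that T0 values are used. The conclusion assumes that the missing figure and the full protocol do not already fix the order. It merits a change because the order cannot be corrected afterwards for an instrument given once.

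**What to change.** - Send the T1 link so that the survey is normally submitted some days before the interview, or at least before any feedback of its outcome. Do not cancel an interview when the survey is outstanding. The change moves the survey; it does not ask for any offer of care to be delayed.
- Record the dates of T1 submission and interview, and whether feedback had been given.
- State which instruments enter the ROC analyses and at which time point. Use the T0 BEDA-Q for accuracy.
- Base the main EDE-Q accuracy analysis on responses given before the interview. Show all responses as a sensitivity analysis, which also reveals whether early and late responders differ.
- Report the convergent-validity and invariance results for the EDE-Q with and without responses given after the interview.

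The cost is slightly more scheduling work and a few EDE-Q responses moved out of the main accuracy analysis. With about 27 expected cases, each one moved matters for precision, so the e-mail timing is the more important part of the change.
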